## Abstract

**Background:**

Today’s children are more overweight than previous generations and physical inactivity is a contributing factor. Modelling and promoting positive behaviour in the early years is imperative for the development of lifelong health habits. The social and physical environments where children spend their time have a powerful influence on behaviour. Since the majority of preschool children spend time in care outside of the home, this provides an ideal setting to examine the ability of an intervention to enhance movement skills and modify physical activity behaviour. This study aims to evaluate the efficacy of the Activity Begins in Childhood (ABC) intervention delivered in licensed daycare settings alone or in combination with a parent-driven home physical activity-promotion component to increase preschoolers’ overall physical activity levels and, specifically, the time spent in moderate to vigorous physical activity.

**Methods/design:**

This study is a single site, three-arm, cluster-randomized controlled trial design with a daycare centre as the unit of measurement (clusters). All daycare centres in the National Capital region that serve children between the ages of 3 and 5, expressing an interest in receiving the ABC intervention will be invited to participate. Those who agree will be randomly assigned to one of three groups: i) ABC program delivered at a daycare centre only, ii) ABC program delivered at daycare with a home/parental education component, or iii) regular daycare curriculum. This study will recruit 18 daycare centres, 6 in each of the three groups. The intervention will last approximately 6 months, with baseline assessment prior to ABC implementation and follow-up assessments at 3 and 6 months.

**Discussion:**

Physical activity is an acknowledged component of a healthy lifestyle and childhood experiences as it has an important impact on lifelong behaviour and health. Opportunities for physical activity and motor development in early childhood may, over the lifespan, influence the maintenance of a healthy body weight and reduce cardiovascular disease risk. If successful, the ABC program may be implemented in daycare centres as an effective way of increasing healthy activity behaviours of preschoolers.

**Trial registration:**

Current Controlled Trials: ISRCTN94022291. Registered in December 2012, first cluster randomized in April 2013.

## Background

The prevalence of child obesity has increased dramatically over the past three decades [1–3] and attenuating these rates is a high priority in Canada, not only from a population health perspective, but from the health care system’s economic perspective. Moreover, obesity tracks very closely from childhood to adolescence to adulthood [2, 4]. Six in ten obese children have at least one risk factor for cardiovascular disease, and an additional 25% have two or more risk factors [4]. Co-morbidities, such as Type 2 diabetes and non-alcoholic fatty liver disease, once considered problems among adults, are now being reported at a greater frequency among youths [5–8]. The greater risk of health complications associated with early morbidity affects normal childhood development and quality of life. In addition, the long-term health care burden increases exponentially if we include the obesity-associated chronic co-morbid conditions. It has been projected that the current generation of children will be the first in modern history to see a shorter life-expectancy than their parents [1] and we know that once it has developed, obesity is very difficult to treat. Indeed, there are many critical periods for intervention over one’s lifespan; however, these findings underscore the importance of prevention early in life and recent mathematical modelling suggests that targeted interventions for young children (0 to 6 years) could yield considerable cost savings to the health care system [9].

Canadian surveillance data, using directly measured heights and weights gathered as part of the Canadian Community Health Survey, indicate that overweight and obesity exist in the preschool age group with 15.2% of children aged 2 to 5 years categorized as overweight and 6.3% as obese [3]. Overweight children have higher risks for numerous health conditions and children who become obese before the age of 6 years are likely to be obese later in childhood [2]. The negative trajectory continues as these children often remain overweight as adults [4]. Physical inactivity is associated with increased risk of several chronic diseases including obesity and heart disease [5, 7] and we know that only 7% of Canadian children between the ages of 6 and 19 years are meeting current physical activity (PA) guidelines [8]. There is considerable evidence to indicate that reduced PA or increased sedentary behaviour are implicated in the etiology of childhood obesity and its associated conditions [6, 9, 10]. From the cardio-metabolic standpoint, the currently available evidence, albeit sparse, indicates that PA during the preschool years is associated with i) more desirable body composition variables [11–16] and ii) decreased cardiovascular risk factor status (i.e., lower total cholesterol [17], higher HDL cholesterol [17, 18], and lower sub-maximal heart rate during exercise [19]). Furthermore, motor development, or the process by which a child acquires movement patterns and skills, has also been shown to be positively associated with PA [20–22]. Early motor development is important as motor skills are a key factor in the likelihood of participation in various forms of PA during later childhood and adolescence [21, 23, 24].

PA is an acknowledged critical component of a healthy lifestyle and childhood experience as it has a meaningful impact on lifelong behaviour and health. Opportunities for PA and motor development in early childhood may, over the lifespan, influence the maintenance of a healthy body weight and reduce the risk of cardiovascular disease. It has been noted that children with low movement competence usually exhibit low PA levels [25, 26] and tend to be vigorously active less often, play less on large playground equipment, and spend less time interacting socially with their peers [25]. Fundamental movement skills (e.g., catching, throwing, jumping, and running) are the essential building blocks for the acquisition of more refined and complicated skills that can be applied later in life, such as sporting, recreational, and physical activities [27–29]. However, movement skills will not develop to their full potential without opportunities to practice in environments that are stimulating and supportive [30, 31]. Butcher and Eaton [26] found that preschoolers’ movement competence was already influencing their PA levels and their PA choices.

### Rationale

There is a paucity of information on current trends in PA of preschool aged children in Canada, [32–34] and on the relationship between the ability of children to perform fundamental movement skills and prediction of PA [35]. A 2012 systematic review was recently performed by Timmons et al. [36] to assemble and interpret the best available evidence for minimal and optimal amounts of PA needed to promote healthy growth and development in young children, including preschoolers. The underlying objective of this review was to help inform the development of evidence-based PA guidelines for this age group. The subsequently published guidelines recommend that “*preschoolers (aged 3–4 years) should accumulate at least 180 min of physical activity at any intensity spread throughout the day, including a variety of activities in different environments, activities that develop movement skills, and progression toward at least 60 min of energetic play by 5 years of age*” [37]. A similar review [38] has also been published advocating that preschool-aged children should not be sedentary for more than 60 minutes at a time (less is better), except when sleeping, and guidelines have since been published [39] to this effect.

More than half of Canadian children between the ages of 6 months and 5 years are enrolled in some form of non-parental care, with a mean of 29 hours per week in this arrangement [40, 41]. Canada fails miserably on an international scale, in comparison to all other Organisation for Economic Co-operation and Development countries, with regard to treatment of our youngest and arguably most vulnerable citizens. According to the UNICEF Report Card, entitled *The Child Care Transition*, which focuses on the shift from parents raising children to out-of-home daycare, Canada was tied for last place in ensuring that this age group is getting high quality out-of-home care [42]; the key criticism of Canada was “*lack of substantial public investment in education until children reach the age of 5*”. This is a critical issue given that Canadian children are now spending more time in care outside of the home than ever before. Recognizing that the landscape of childcare in the developed world has changed dramatically over the last two decades, with the vast majority of children now attending some form of daycare during their early years, the preschool environment represents a focal point with great promise for health interventions. Several groups throughout the world have similarly identified the need to encourage and support PA within the preschool curriculum [43–45] and various teams are working towards evaluating potential solutions [46–51]. Uniquely, this Canadian three-arm RCT study is poised to explore not only changes in PA and anthropometrics, but motor skill development and quality of life, as well as changes to the daycare environment and to identify if the addition of a home component results in greater benefits.

We know that i) physical inactivity and poor fitness are independent risk factors for obesity, metabolic disorders, and cardiovascular disease in youth, ii) successful development of motor skills provides stimulus for ongoing PA engagement contributing to long-term health [52], and iii) PA levels track from early childhood to adulthood. Consequently, increasing children’s PA levels in the preschool years may alter their activity trajectory and increase the likelihood they will be physically active throughout development stages and into adulthood. The proposed intervention, Activity Begins in Childhood (ABC), is clinically relevant as it includes training workshops for daycare-providers focusing on the importance of PA and reducing sedentary behaviour, as well as strategies for implementing a variety of structured and unstructured physical activities to meet these objectives. This study will be able to address how viable the daycare setting is to promote PA in preschool-aged children and the possible incremental value of the home setting.

## Methods/design

### Study objectives

The primary objective of this study is to evaluate the efficacy of the ABC intervention program delivered in licensed daycare settings alone (intervention, daycare (DC)) vs. standard daycare curriculum (comparison (COM)) to increase preschoolers overall PA levels, specifically time spent in moderate to vigorous physical activity (MVPA).

The secondary objectives aim:

 To evaluate the potential additive contribution of a parent-driven home PA-promotion in addition to the daycare provider-facilitated intervention on its own (i.e., intervention DC vs. DC + HOME) To evaluate the efficacy of the ABC intervention arms to decrease the amount of time spent in sedentary behaviour To evaluate the effects of the ABC intervention arms on fundamental and gross motor skills in preschoolers attending daycare centres To evaluate the effects of the ABC intervention arms on preschool children’s anthropometrics, such as height, weight, body mass index, lean body mass, fat mass, and percent body fat To assess the effects of the ABC intervention on daycare providers’ attitudes, control beliefs, perceived competency, and intentions toward incorporating PA into the daycare curriculum, and examine whether these social-cognitive variables impact PA in children To evaluate the effects of the ABC intervention on child’s quality of life and on the quality of life of the parents as well To evaluate the costs of delivering the ABC intervention with the outcomes achieved to provide a valuable analytical framework to guide decision making by those who are responsible for allocating resources

### Hypotheses

We hypothesize that MVPA (minutes/day) will be greater in the combined DC + HOME arm when compared with the DC-only arm, but that MVPA will be greater in both intervention groups vs. the COM group. We believe both intervention arms will show larger reductions in sedentary behaviour and greater improvements in fundamental and gross motor skills, body composition, and quality of life at the 6-month follow-up compared to the COM arm, with the combined intervention (DC + HOME) being superior. We predict that the ABC intervention will enhance providers’ and parents’ attitudes, control beliefs, perceived competency, and intentions to increase children’s PA in the daycare setting and home environment immediately following the training workshop, and consistent with the theory of planned behaviour, these process measures will predict children’s PA at follow-up.

### Trial design

We are carrying out a single site, three-arm, cluster-randomized controlled trial design in Canada’s National Capital Region, with daycare centres as the unit of measurement (clusters) to evaluate the efficacy of the ABC intervention and training manual to increase PA (Figure 1).

**Figure 1 Fig1:**
[figure not shown]
**CONSORT flow diagram.**

### Participants, inclusion/exclusion, and recruitment

#### Daycare centres

All licensed daycare centres in the National Capital Region (NCR) that serve children between the ages of 3 and 5, with an enrolment of >20 children in this age range, and provide service in either English or French, are eligible to participate. Daycare recruitment will commence with an initial letter mailed out to the directors of all daycare centres within the NCR, requesting that the directors contact the research coordinator for further information related to the study if they are interested in taking part. Daycare directors who agree for their site to participate in the trial are committing to modify their curriculum accordingly and support their staff in facilitating the required changes if they are randomized to the intervention arm and control groups must agree to allow study personnel to visit their facilities for planned assessments.

#### Preschoolers

All preschool children between the ages of 3 and 5 years attending the involved daycare centres, who plan to remain within the respective daycare setting for at least 6 months, and whose parents speak either English or French, will be eligible to participate regardless of mental or physical capabilities. While the daycare environment will be subjected to the intervention, only children whose parents sign informed consent will be assessed.

### Ethics and consent

The study has been approved by the Research Ethics Board at the Children’s Hospital of Eastern Ontario Research Institute (REB protocol number: #12/158X). The daycare centres which meet the study inclusion criteria will be sent an information sheet and asked to indicate their desire to participate by providing written consent to the research coordinator. Following daycare director consent, parents of the potential participants will be approached via letter, poster, and word of mouth. Interested participants will provide a letter of informed consent to the research coordinator. Participants involved with the home intervention and daycare providers involved with the intervention will be reimbursed for their time with a $50 (Canadian dollars) gift certificate to a local grocery store chain.

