### Randomization

Eighteen daycare centres (clusters) that agree to participate will be randomly assigned to one of three groups: i) ABC program delivered at daycare centre only (n = 6; DC), ii) ABC program delivered at daycare plus a home component (n = 6; DC + HOME) or, iii) regular daycare curriculum (n = 6; COM).

Because daycare centre size, language of delivery, and season may influence the outcomes of interest, randomization will be stratified based on these variables. Small-medium daycare centres will be defined as those serving 10 to 20 children in our 3- to 5-year-old targeted age range, those enrolling 21 or more preschoolers will be considered large. To take into account possible seasonal effects on PA, the trial will be stratified by season: 8 sites will be randomized in the Spring of 2013 (3 in DC, 3 in DC + HOME, and 2 in COM)), 7 in the Fall of 2013 (2 in DC, 2 in DC + HOME, and 3 in COM), and 3 will be randomized in the Fall of 2014 (1 in DC, 1 in DC + HOME, and 1 in COM). The randomization sequence will be computer generated by a data manager at the Clinical Research Unit at the Children’s Hospital of Eastern Ontario, who is not affiliated with this trial. Before running the randomization program, the data manager will document the study ID and daycare centre size, and season. After running the program, the data manager will document the group assignment and then inform the study coordinator of the assignment. To ensure adequate allocation concealment, the randomization sequence list will be kept centrally with the data manager at the Clinical Research Unit. It will not be accessible to members of the study team and subjects and only be activated when a centre is eligible to be randomized.

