**Table 1 Tab1:** **Outcome assessments**

Activity Begins in Childhood (ABC)											
	Group 1: DC				Group 2: DC + HC				Group 3: COM		
	B	PW	3 mos.	6 mos.	B	PW	3 mos.	6 mos.	B	3 mos.	6 mos.
Consent Form	√				√				√		
Socio-Demographic Questionnaire	√				√				√		
Physical Activity Monitor Log	√		√	√	√		√	√	√	√	√
Environment Questionnaires					√		√	√			
EPAO	√		√	√	√		√	√	√	√	√
Gross Motor Assessment	√		√	√	√		√	√	√	√	√
Anthro Measures & Body Composition	√		√	√	√		√	√	√	√	√
Workshops/Webinar	√				√						
Workshop/Webinar Questionnaires	√	√		√	√	√		√			
Quality of Life Questionnaires	√		√	√	√		√	√	√	√	√
Pregnancy and Lifestyle Questionnaire	√				√				√		

B, baseline; mos, months; PW, post workshop; EPAO, Environment and policy assessment and observation.

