## Trial status

Baseline data were collected for the initial cohort in April 2013. The 6-month follow-up data were collected in October, 2013. The second cohort was randomized in November of 2013 with 6-month follow-up taking place in May 2014. Randomization of a third cohort is planned for September 2014.

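### Nothing in the protocol makes a centre's allocation wait for parental consent or baseline accelerometry, so selective enrolment is a risk, and the primary model does not adjust for baseline MVPA.

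*Protocol article*

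**What the plan says.** **Allocation.** Under Randomization, "Eighteen daycare centres (clusters) that agree to participate will be randomly assigned to one of three groups". The sequence will "only be activated when a centre is eligible to be randomized", and the data manager will then "inform the study coordinator of the assignment". Eligibility under Daycare centres is set at centre level (licence, age range served, enrolment, language).

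**Parental consent.** Under Ethics and consent, "Following daycare director consent, parents of the potential participants will be approached via letter, poster, and word of mouth", and "Interested participants will provide a letter of informed consent to the research coordinator". Under Preschoolers, only children with parental consent are assessed.

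**Baseline.** The Comparison section places baseline 2 weeks before the provider workshops and parental webinars. It gives no position relative to randomisation. It includes in that measurement the home environment as parents see it, and the attitudes and intentions of providers and parents.

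**Forms by arm.** In the baseline column of Table 1, the row "Environment Questionnaires" is ticked for DC + HOME only. The workshop/webinar questionnaires are ticked for DC and DC + HOME but not for COM. The Questionnaires section likewise gives the pre-training attitude form to intervention providers and parents.

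**Analysis.** The primary model compares MVPA at 6 months between DC and COM with a random daycare effect, adjusting for age, sex and extra-curricular activity. Baseline activity enters only under Secondary analyses.

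**Dates.** Trial registration dates the first cluster randomisation to April 2013, and Trial status dates the first cohort's baseline to the same month. Trial status adds: "The second cohort was randomized in November of 2013 with 6-month follow-up taking place in May 2014" and "Randomization of a third cohort is planned for September 2014".

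**The concern.** Centres are randomised, but the children analysed are those whose parents agree. If parents, providers or the person collecting consent know the arm by then, the arms may enrol children who differ in activity. Randomising centres does not protect against that, and neither does a random effect for daycare, which deals with correlation within centres and not with differences in who entered. Concealing the sequence protects the assignment of a centre. It does not protect recruitment of children inside a centre already assigned.

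A difference created in this way would pass into the primary estimate, apart from whatever age, sex and extra-curricular activity absorb, because baseline MVPA is not in the primary model. If providers know their arm before the accelerometers are worn, baseline MVPA may itself be affected, which would weaken the secondary covariance analysis too.

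**Working it through.** **Order of events, from the text**

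| Step | Stated trigger | Tied to the other steps? |
|---|---|---|
| Centre allocated | Centre agrees and is eligible | No mention of parental consent or baseline |
| Coordinator told the arm | Randomisation program has run | Not delayed |
| Parents approached | Director has consented | No mention of allocation |
| Baseline measured | 2 weeks before training | No mention of allocation |

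The stated triggers allow allocation before or after consent and baseline.

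**Does the text lean one way?** The Comparison section puts the attitude and home-environment assessments inside the baseline measurement, 2 weeks before training. Table 1 and the Questionnaires section give the corresponding forms only to intervention arms. Taken together, these suggest that the arm is known when baseline is measured. The month-level dates settle nothing: April 2013 for both events in the first cohort, and November to May in the second, fit either order.

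**The plan's own figure.** Sample size gives 6 centres per group for 80% power, 15 min/day, 5% type I error, 15 children per centre and ICC 0.08. No SD is stated, so the figure cannot be reproduced directly. The SD it implies is:
- Design effect: 1 + (15 − 1) × 0.08 = 2.12.
- Effective children per arm: 6 × 15 / 2.12 = 42.45.
- Implied SD (normal): 15 / [(1.960 + 0.842) × √(2/42.45)] = 24.7 min/day. With a t distribution on 10 df it is 22.2.
- Standard error of the difference at SD 24.7: 24.7 × √(2/42.45) ≈ 5.35 min/day.

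**Illustrative size of selection.** Let willingness to consent and MVPA be jointly normal with correlation r. If a fraction p consents, the mean among consenters is raised by r × SD × λ(p), with λ(p) = φ(z_p)/p. The values are λ(0.75) = 0.424, λ(0.60) = 0.644, λ(0.70) = 0.497 and λ(0.50) = 0.798. The shift between arms is r × SD × the difference in λ, for SD 22.2 to 24.7:

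| Consent in the two arms | Difference in λ | r = 0.1 | r = 0.3 |
|---|---|---|---|
| 75% vs 60% | 0.220 | 0.49 to 0.54 min/day | 1.47 to 1.63 min/day |
| 70% vs 50% | 0.301 | 0.67 to 0.74 min/day | 2.01 to 2.23 min/day |

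Against 15 min/day this is 0.49/15 = 3% to 2.23/15 = 15%. The consent rates and r are assumptions; the document gives neither.

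**Effect on type I error.** With no true effect, a shift b gives a two-sided error of 1 − Φ(1.96 − b/5.35) + Φ(−1.96 − b/5.35). For b = 2 this is 6.6%, and for b = 3, already above the range in the table, 8.7%.

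**The case against.** The strongest case against is that no sentence says allocation comes first. Parents are approached after director consent, not after randomisation, and the condition of being eligible for randomisation could include completed consent and baseline. The flow diagram, which might show the order, is not in the copy reviewed, and an article condenses procedure. All of this stands. It is why the point is a risk and not an established fault.

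A reader might infer more than the documents support:
- *That the arm-specific forms prove accelerometry followed allocation.* They do not. The same Table 1 column also holds the workshops and webinars, and the Questionnaires section times the attitude form only as before training. A training-day hand-out fits those two places, but not well the Comparison section, which puts the attitude and home-environment assessments in the baseline measurement. The suggestion stands; the proof does not. The environment row also concerns only DC + HOME, which is outside the primary comparison.
- *That randomisation and baseline coincided in the second cohort.* Dates given by month cannot show this.
- *That the person told the arm also collects consent.* One section names a study coordinator and the other a research coordinator. They may be different roles.
- *That the last centre's arm is predictable from the one-per-arm quota in the third cohort.* This holds only if centres are activated one at a time, and it concerns centre assignment rather than consent.

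The mechanism is also weaker for DC versus COM than for the home arm. Children in a DC centre receive the programme whether or not their parents consent to assessment, and DC parents have no webinar and no stated gift certificate. Adjustment for extra-curricular activity may absorb part of any difference, and the accelerometer limits assessor bias. These points reduce the likely size. They do not supply the missing safeguard.

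**Conclusion.** As written, the plan leaves open that a centre's arm is known before its parents consent and before baseline is measured, and its baseline forms lean towards that order. The conclusion goes no further: whether it happened in the first two cohorts cannot be told from the article.

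The size is unknown and probably modest. The range of 0.5 to 2.2 min/day rests wholly on the assumed consent rates and correlations, joint normality, and an SD back-solved from the stated power. At a shift of 2 min/day, type I error would be near 6.6% instead of 5%. Larger distortions would need stronger selection than was assumed here. The point still merits action, because the remedy is cheap, one cohort is still to be randomised, and the trial already collects the baseline MVPA that its primary model leaves out.

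**What to change.** 1. **Third cohort.** State that parental consent is closed and baseline accelerometry complete in all three centres before any of their allocations is released, and that the three are then released together. This also removes any predictability from the quota.
2. **First two cohorts.** Report, by arm, the numbers of children eligible, approached and consented, and whether consent and baseline preceded allocation.
3. **Primary analysis.** Make the baseline-adjusted mixed model primary, in place of the 6-month comparison without baseline MVPA. Say plainly that it corrects selective enrolment only in part, and that it assumes baseline was not itself altered by knowledge of the arm. Record the change before outcomes are compared by arm.

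**Cost.** A short delay in releasing allocation for three centres, and loss or imputation of children without valid baseline wear. The planned number of centres and children does not change.
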